## Abstract

**Background:**

Exercise training in hemodialysis patients improves fitness, physical function, quality of life and markers of cardiovascular disease such as arterial stiffness. The majority of trials investigating this area have used supervised exercise training during dialysis (intradialytic), which may not be feasible for some renal units. The aim of this trial is to compare the effects of supervised intradialytic with unsupervised home-based exercise training on physical function and arterial stiffness.

**Methods and design:**

This is a randomised, controlled clinical trial. A total of 72 hemodialysis patients will be randomised to receive either six months of intradialytic exercise training, home-based exercise training or usual care. Intradialytic patients will undergo three training sessions per week on a cycle ergometer and home-based patients will be provided with a walking program to achieve the same weekly physical activity. Primary outcome measures are six-minute walk distance (6 MWD) and aortic pulse wave velocity (PWV). Secondary outcome measures include augmentation index, peripheral and central blood pressures, physical activity and self-reported health. Measures will be made at baseline, three and six months.

**Discussion:**

The results of this study will help determine the efficacy of home-based exercise training in hemodialysis patients. This may assist in developing exercise guidelines specific for these patients.

**Trial Registration:**

ACTRN12608000247370

## Background

A number of studies have shown that intradialytic exercise training has positive effects on patients, such as improving cardiorespiratory fitness, physical function and self-reported health [1]. Less work has focussed on the effects of exercise training on cardiovascular risk factors in dialysis patients although some evidence suggests improvements in fasting glucose and insulin, an enhancement in the management of hypertension, and a reduction in inflammation [2-5].

Cardiovascular pathologies observed in ESKD patients include left ventricular hypertrophy and arterial disease [6]. In addition to the characteristic lesions of atherosclerosis, dialysis patients also experience thickening and fibrosis of the arterial wall in response to pressure and volume overload, loss of elastic fibres and medial fibrosis [7]. Such arterial remodelling, along with medial calcification, causes arteries to stiffen, thereby exacerbating left ventricular dysfunction [8]. Indeed, widening of the pulse pressure, the simplest and crudest method of assessing arterial stiffness, has proven to be a better marker of mortality than systolic pressure in haemodialysis patients [9]. Stiffening also results in more rapid propagation of the arterial pulse pressure wave through the conductance arteries and can be readily assessed by measuring aortic pulse wave velocity (PWV; a marker of regional large artery stiffness) and central augmentation index (AIx; a composite marker of systemic arterial stiffness and left ventricular systolic loading). Indeed, there is a clear evidence base that measures of arterial stiffness are independent predictors of cardiovascular morbidity and mortality in different patient populations [10] but particularly in ESKD patients [11-13].

To date, to our knowledge, only two studies have investigated the effect of exercise training on arterial stiffness in ESKD [14,15]. In an uncontrolled study of 11 hemodialysis patients, Mustata and coworkers [14] found a significant improvement in AIx after three months of supervised exercise training. More recently, aortic PWV was significantly decreased following three months of intradialytic exercise in 19 hemodialysis patients [15].

The majority of studies investigating the effects of exercise in dialysis patients have used supervised intradialytic exercise training. These programs are resource intensive which may preclude their use in clinical practice. Consequently other interventions should be investigated. To our knowledge only one study has compared different training regimens in an attempt to optimize the benefits of exercise training in ESKD patients [16]. Therefore, the aims of this study are to compare the effects of supervised intradialytic or unsupervised home-based exercise training on arterial stiffness and physical function in hemodialysis patients.

## Methods

### Study design and setting

The study is a multi-centre, randomized controlled trial in hemodialysis patients. The study will be conducted at the Launceston General Hospital and Burnie Satellite Renal Units in Northern Tasmania and the Hobart Renal Unit, which, combined, service a population of approximately 485,000.

### Ethical considerations

The Tasmanian Statewide Scientific and Ethics Committees have approved the trial. The Ethics Committee will be provided with annual reports of the trial progress and will promptly receive all adverse event reports. A condition of ethical approval requires investigators to provide brochures to all hemodialysis patients at each of the sites indicating the benefits of exercise in end stage kidney disease. Hence, potential benefits of regular exercise will be made known to patients regardless of their decision to participate in the study or the group to which they are randomised.

### Identification of eligible patients

Patients who commence and/or maintain dialysis for at least three-months will be approached to participate in this study. Eligible patients will receive a copy of the patient information sheet placed in the medical record. The principal investigator will then explain the study during a clinical consultation. After the explanation the subjects will be provided with a patient information sheet and informed consent form. The subject will then be asked to take this away with them and make a decision before their next hemodialysis visit. If the subject agrees to participate, they will sign the consent form with an independent person signing as a witness.

### Eligibility

Inclusion criteria are; age >18 and < 85 years incident and/or prevalent dialysis patients. Subjects will be excluded if they have unstable angina, lower limb amputation, or if they already meet or exceed the exercise recommendation of 120 minutes of moderate intensity physical activity per week[17] Subjects will also be excluded if they are participating in, or propose to participate in, another clinical intervention study within 30 days prior to study entry.

### Randomization

An individual not associated with the trial will perform the randomization using a computer generated random number system.

### Interventions

Intradialytic training requires participants to train on cycle ergometers (Rehab Trainer 881E, Monark, Sweden) within the first two hours of each dialysis session, three times per week for 6 months. Intensity will be individualised on the basis of perceived exertion, exercise heart rate and blood pressure. Participants will be requested to exercise at an RPE of 12–13 on the Borg 6–20 scale [18]. In cases where patients' training heart rates are low at a reported RPE of 12–13, the supervisor will increase the resistance to elicit a greater cardiorespiratory response. However, patients will be permitted to stop and rest or request to train at a lower intensity. In the event that exercise blood pressure exceeds predetermined safe levels for the participant, (>200/110 mmHg) they will be instructed to temporarily cease exercise and will be monitored until blood pressure returns to safe levels. Patients on medications that affect cardiac sinus rhythm will be trained strictly according to reported RPE. Over the duration of the exercise intervention, supervisors will periodically increase the resistance of the ergometer to maintain RPE. While participants will be encouraged to start and progress the duration of exercise according to their individual capabilities, a general guideline used by investigators will be for participants to complete fifteen minutes of exercise per session in the first two weeks of the intervention, progress to thirty minutes of exercise per session by week 12 and to forty-five minutes by week 24. Power output (w) and duration (minutes) of each exercise session will be recorded to estimate participants' individual energy expenditure per session during the training period.

Home-based participants will be asked to perform thrice weekly unsupervised walking for six months at perceived exertions of 12–13 on the Borg 6–20 scale. To ensure a similar treatment to the intradialytic group's training duration, home-based participants will be requested to start and progress their walking program according to individual capabilities however investigators will encourage participants to start at fifteen minutes per session for the first two weeks and to progress to 30 minutes by week 12 and to forty-five minutes by week 24 as per the ID group. Participants will be phoned fortnightly to provide encouragement and to allow feedback on progress. Only the duration and number of steps of each walking session will be monitored and, therefore, an adequate estimation of total energy expended will not be performed. However, HB participants will be encouraged to regularly increase intensity by walking faster or walking on routes with some degree of incline. Usual care participants will be requested to maintain their usual daily activities and will be reminded of the importance of this regularly throughout the study.

Once randomised, participants will undergo a series of tests including physical function and arterial stiffness measurements at baseline, three months, and six months. All participants will be instructed to refrain from physical activity for 24 hours and food and caffeine intake for three hours prior to each testing session.

### Primary objectives and primary outcome measures

The primary objectives are to compare the effects of supervised intradialytic and home-based exercise training on physical function and arterial stiffness. The primary outcome measures will be outlined below. The hypothesis is that supervised training will be superior to home-based training because the patients will be more likely to meet physical activity guidelines when supervised.

### Physical function

Physical function will be assessed by the 6-Minute Walk Distance (6 MWD) test. This will be performed along a 25-metre stretch of walkway in a quiet hospital corridor. Prior to the test, all participants will undergo a short warm up and familiarisation with the walkway. Participants will be instructed to walk as far as they can during the six minutes. Participants will be allowed to stop and rest if needed and will receive regular encouragement from the investigator throughout the test. Participants, but not investigators, will be blinded to all previous test results.

The secondary outcome measure for physical function is the Timed-Up & Go (TUG) test. The time taken for participants to stand from a seated position, walk 3-metres, turn, and walk back to a chair, and return to the seated position as quickly as possible, is recorded. The better of two attempts will be recorded.

### Arterial stiffness

All measures of arterial stiffness will be taken in the hour preceding dialysis. Aortic (carotid-femoral) pulse wave velocity (PWV) is the primary outcome measure for arterial stiffness. The method involves electrocardiogram-gated sequential applanation tonometry (SPT-301 Mikro-Tip, Millar Instruments, Houston, Texas) of the common carotid and femoral (groin) arteries using the foot-to-foot method (SphygmoCor 7.01, AtCor, Sydney, Australia) as previously described [19].

Additional secondary outcome measures include peripheral (carotid-radial) PWV, AIx and central blood pressures. Peripheral PWV will be assessed as described above from waveforms acquired at the common carotid artery and radial artery. Central blood pressures and AIx will be estimated by pulse wave analysis (PWA) involving radial applanation tonometry performed on the non-fistula arm using customised software (SphygmorCor 7.01, AtCor, Sydney, Australia) with a validated [20] and reproducible [21] generalized transfer function. In patients with a fistula in both arms, the brachial artery (medial to biceps) of the dominant arm will be used. The AIx is defined as the difference between the 2^nd ^and 1^st ^central systolic peaks expressed as a percentage of central pulse pressure[22] Since AIx is influenced by heart rate, the SphygmoCor software also incorporates an algorithm which adjusts AIx to a standard heart rate of 75 beats per minute (bpm) [23]. The central waveform will be calibrated by the average of two measures of automated brachial blood pressure by sphygmomanometry (UA-767, A&D, Saitama, Japan) after five minutes of supine rest.

### Physical activity and self-reported health

Additional secondary outcome measures include physical activity and self-reported health. Items from the Active Australia Questionnaire [24] will be used to quantify the physical activity performed by participants as previously described [25]. Briefly, participants in the exercise groups will be requested to include any training performed in the previous week as part of the study in their response to the questionnaire. The survey measures frequency, intensity and duration of incidental and/or intentional physical activity in the week prior to the time of testing. The total time spent in each activity will be multiplied by an intensity value (3.5 [light], 4 [moderate] and 7 [vigorous]) and used to calculate participants' weekly physical activity in MET.min^-1^.

Self-reported health will be evaluated using the Medical Outcomes Short-Form 36-items (SF-36) Health Survey [26]. Widely used previously in HD populations [27,28] it includes eight independent scales and assesses physical and mental dimensions of health.

**Figure 1 F1:**
[figure not shown]
**Flow chart of trial**.

### Visits two and three

These visits will occur at approximately three and six months after baseline. Measures and the sequence of these measures will be identical to the baseline visit.

### Adherence to exercise training

Adherence to exercise protocols will be assessed by auditing training diaries. The supervisors will complete the intradialytic participants' training diaries at each training session. Home-based participants will complete diaries themselves and return them at the testing sessions.

### Withdrawal from study

Subjects will be withdrawn from the study at their request, without prejudice, as documented and explained at the time of consenting. Patients who withdraw will be invited to consent to follow-up testing for the remainder of the trial to enable an intention to treat data analysis.

### Sample size calculation

Data from other studies indicates that 6 MWD has the highest variability of the two primary outcome measures (mean ± SD; PWV = 11.1 ± 3.2 [29], 6 MWD = 347 ± 147 m[30]). We assume that this will also mean that changes in 6 MWD will be more variable than changes in PWV. We then assume that a 10% improvement in 6 MWD will be clinically significant. Therefore, with alpha = 0.05, and beta = (1-0.1 = 0.9) we require 17 subjects per group. Allowing for a 20% withdrawal rate we aim to recruit 20 patients per group.

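### The sample size does not tie its 10% effect on 6 MWD to the supervised-versus-home hypothesis, and on the printed SD the power for that contrast is about 10%, not 90%

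*Protocol article*

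**What the plan says.** Primary objectives and primary outcome measures sets the question: "The primary objectives are to compare the effects of supervised intradialytic and home-based exercise training on physical function and arterial stiffness". One hypothesis follows: "The hypothesis is that supervised training will be superior to home-based training". The reason given is that supervised patients are more likely to reach activity guidelines. No size of difference is attached to it.

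Under Interventions, the home arm has the same perceived-exertion target, three sessions a week, and a duration schedule meant to "progress to 30 minutes by week 12 and to forty-five minutes by week 24 as per the ID group".

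The Sample size calculation quotes 6 MWD as 347 m with SD 147 m from another study. It adds "We assume that this will also mean that changes in 6 MWD will be more variable than changes in PWV", then "We then assume that a 10% improvement in 6 MWD will be clinically significant", then "with alpha = 0.05, and beta = (1-0.1 = 0.9) we require 17 subjects per group". It names no contrast, test, sidedness or SD of change. It ends with "Allowing for a 20% withdrawal rate we aim to recruit 20 patients per group", whereas the abstract has 72 patients in three groups, which is 24 each if allocation is equal.

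**The concern.** A power statement belongs to a particular contrast, a particular difference and a particular SD. Here the contrast is left open, and the difference is never stated or justified as supervised minus home-based. That matters because the comparator is an active programme with a matched prescription. The gap between the arms is the supervised gain minus whatever the home walkers gain, so any home benefit shrinks it.

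The implied 90% also has to be checked against the mean and SD printed beside it, because a reader will apply it to the stated hypothesis. If the true power is far lower, a null supervised-versus-home result could be taken as good evidence that the cheaper programme is as effective. The Discussion points towards exercise guidelines and cost-effective delivery, so that misreading would have consequences.

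**Working it through.** **Inputs from the Sample size calculation:** mean 347 m; SD 147 m; effect 10%, so 0.10 × 347 = 34.7 m; alpha 0.05; beta printed as 0.9; 17 per group. **Assumptions:** two-sided test, two independent groups of equal size, no losses.

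**1. Reproducing 17.** For two means, n per group = 2 × [SD × (z for alpha + z for power) / difference]².

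- Beta taken literally as 0.9 (power 0.10): 2 × [147 × (1.960 − 1.282) / 34.7]² = 16.5, rounded up to **17**. This matches the article.
- Power 0.90 (beta 0.10): 2 × [147 × (1.960 + 1.282) / 34.7]² = 377.1, rounded up to **378**.
- Other readings on SD 147 m also miss 17. At 90% power, a one-sided two-group test needs 308, and a one-sample or paired test needs 189 (two-sided) or 154 (one-sided). At 80% power, the two-sided two-group figure is 282.

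**2. Power for supervised versus home-based, SD 147 m.** The standardised shift is difference / (147 × √(2/n)). At n = 17 and 34.7 m it is 34.7 / 50.4 = 0.688, and the chance of exceeding 1.960 is 10.2%.

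| Per group | Power for 34.7 m | Power for 17.35 m (half, assumed) |
|---|---|---|
| 17 | 10.2% | 5.3% |
| 20 | 11.2% | 5.6% |
| 24 | 12.7% | 6.0% |

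These count rejections in favour of supervised training. Including the opposite tail, the half-effect figure at 17 per group is about 6.4% (6.3% with the t distribution). At 90% power, a 17.35 m difference needs 1509 per group.

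**3. Could an SD of change rescue 17?** Solving the formula for SD at 17 per group and 90% power gives 34.7 × √(17/2) / 3.242 = 31.2 m; the t distribution gives 30.3 m. Since SD of change = 147 × √(2(1 − r)), that needs a baseline-to-follow-up correlation r of about 0.98. The article gives no correlation, so a range is shown:

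| Assumed r | SD of change | n per group for 90% at 34.7 m | Power at 17 per group |
|---|---|---|---|
| 0.7 | 114 m | 227 | 14% |
| 0.8 | 93 m | 151 | 19% |
| 0.9 | 66 m | 76 | 34% |

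**4. Difference detectable with 90% power at 17 per group.** The two-sample t-test needs a standardised difference of 1.147, and 1.147 × 147 = **169 m**, about half of the 347 m mean (169 / 347 = 49%). The normal approximation gives 147 × √(2/17) × 3.242 = 163 m.

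**The case against.** The strongest reply is that the article never says the 10% is anything other than a between-arm difference. A clinically significant difference is a legitimate target for any contrast, without being a forecast of the gain. The match of 17 with a two-group formula suggests that two arms were compared, and these could be the two exercise arms. The article also gives a reason to expect a gap, since home sessions are unsupervised and only the requested schedule is matched. All of this stands. It limits the point to saying that the 10% is not stated or justified as supervised minus home-based.

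A reader might go further and infer from the word improvement that the 10% is a gain over baseline or usual care, so that the 90% power is sound but belongs to that other contrast. The documents do not support this. No contrast is named, and on the printed SD no comparison between two arms has 90% power for 34.7 m.

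The same reader might grant 90% at 17 per group and scale it down, obtaining 68%, 37% or 13% if home training achieves 25%, 50% or 75% of a 10% supervised gain. That arithmetic is right, but it needs an SD near 30 m that the article does not give, and fractions that it does not state.

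A condensed article may leave details to a full protocol. This one, however, prints its inputs and its result, and the two do not fit together at 90% power.

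**Conclusion.** The point holds in limited form. The article does not connect its 10% effect with its only stated hypothesis, and the implied 90% power is not supported for that hypothesis. On the printed SD, power is about 10% to 13% over the group sizes the article mentions (17, 20, and 24 if 72 are split equally), even if the whole 34.7 m separates the two exercise arms. It is lower if home training yields part of the gain.

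These figures assume a two-sided two-group comparison on an SD of 147 m. Change-score analysis with correlations of 0.7 to 0.9 raises power at 17 per group only to 14% to 34%. That beta and power were interchanged in the calculation is an inference from the printed expression and the match at 16.5; the article does not say so.

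**What to change.** Rewrite the Sample size calculation to:

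- name supervised versus home-based 6 MWD at six months as the contrast;
- give the target difference in metres and why it is a worthwhile difference between two exercise programmes;
- state the SD, or the SD of change with its source, and the sidedness;
- write power as 1 − beta, with the two values the right way round;
- replace the implied 90% with the actual power, or the detectable difference, at the planned size (about 169 m at 17 per group with SD 147 m).

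If an SD of change near 30 m was used, print and justify it. Do not move the 90% to supervised versus usual care, because the printed inputs do not support it there either. Add a sentence that a null supervised-versus-home result will not be read as equivalence.

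The cost is one paragraph and a much less favourable power statement. The correction itself requires no further recruitment, but at the planned size the trial could not claim 90% power for 34.7 m on the printed SD.

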### Statistical analyses

All statistical analyses will be performed using STATA statistical software (STATA 10; Statistical data analysis; Stata Corp; College Station; Texas, USA). Baseline and descriptive data between the groups will be analysed with one-way ANOVA. Binary categorical data will be analysed for variability between the groups using logistic regression. Parametric longitudinal data analysed via two-factor (group, time) analysis of variance (ANOVA) with repeated measures on time using general linear modeling. Weekly physical activity (MET.min^-1^) will be analysed via general linear modelling. Where statistically significant differences are identified, post hoc testing will be performed using Holms tests to locate the means that are significantly different. Statistical significance will be set at p < 0.05.

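### The sample size of 17 per group does not follow from the protocol's own figures, which need about 378 per group for 90% power; beta and power were probably swapped

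*Protocol article*

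**What the plan says.** The Sample size calculation section gives literature values for both primary outcomes: 11.1 ± 3.2 for aortic PWV and 347 ± 147 m for 6 MWD. It selects 6 MWD as the more variable measure and carries this over to changes: "We assume that this will also mean that changes in 6 MWD will be more variable than changes in PWV". The effect is set by "We then assume that a 10% improvement in 6 MWD will be clinically significant". The conclusion is then drawn directly: "Therefore, with alpha = 0.05, and beta = (1-0.1 = 0.9) we require 17 subjects per group". Recruitment follows from it: "Allowing for a 20% withdrawal rate we aim to recruit 20 patients per group".

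Three other places bear on the calculation:

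- Abstract, Methods and design: "A total of 72 hemodialysis patients will be randomised to receive either six months of intradialytic exercise training, home-based exercise training or usual care".
- Primary objectives and primary outcome measures: "The hypothesis is that supervised training will be superior to home-based training".
- Statistical analyses: "Parametric longitudinal data analysed via two-factor (group, time) analysis of variance (ANOVA) with repeated measures on time using general linear modeling".

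The article gives no SD of change, no within-patient correlation and no sidedness for alpha. It does not say whether the 10% is a change within a group or a difference between two groups.

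**The concern.** The section presents 17 as the result of the inputs printed just before it. An effect of 34.7 m against an SD of 147 m is a standardised difference of only 0.24, and no usual calculation detects that with 90% power in 17 patients per group. The label on the error rate is also wrong: 0.9 is the intended power, and beta is 0.1.

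At stake is the trial's claim about what it can detect. The main hypothesis compares two active arms, and the discussion hopes to inform exercise guidelines. A reader told that the trial has 90% power for a 10% gain would give a non-significant result more weight than the printed figures allow.

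**Working it through.** **Inputs** (Sample size calculation section): mean 347 m; SD 147 m; effect δ = 0.10 × 347 = 34.7 m; alpha 0.05, taken as two-sided; intended power 1 − 0.1 = 0.9.

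**1. The plan's figure with the intended power.** For two equal groups, n per group = 2 (SD/δ)² (z₁₋α/₂ + z_power)².

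- 2 × (147/34.7)² = 2 × 17.95 = 35.89
- (1.960 + 1.282)² = 10.51
- n = 35.89 × 10.51 ≈ 377.1, so 378 per group (a t-test calculation gives 378.1)

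The stated 17 is not reproduced. Other variants at SD 147 m do not reach it either:

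| Variant | n |
|---|---|
| One-sided alpha, 90% power | 308 per group |
| Two-sided, 80% power | 282 per group |
| One-sample or paired test using SD 147 m, two-sided, 90% power | 189 |

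**2. The same formula with power 0.10**, which is what beta = 0.9 means literally. Now z_power = −1.282:

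- (1.960 − 1.282)² = 0.460
- n = 35.89 × 0.460 ≈ 16.5, rounded up to 17

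This is the stated figure exactly.

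**3. Power on the printed inputs** (two-sided t-test, δ = 34.7 m, SD 147 m): 10.2% at 17 per group, 11.3% at 20 and 12.6% at 24 (72/3). A three-group F test with one group differing by 34.7 m gives 9.7% at 17.

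**4. What SD of change would make 17 correct?** With 17 per group, 90% power needs a standardised difference of about 1.147 (t-test), so SD = 34.7/1.147 ≈ 30.3 m. From SD_change = 147 √(2(1 − r)), r = 1 − (30.3/147)²/2 ≈ 0.98. If the 10% is read as a pre-post change within one group, the SD of change would have to be about 41.4 m, r ≈ 0.96.

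**5. Change-score power under assumed correlations.** The values of r are assumptions; the protocol gives none. Two-sided t-test, δ = 34.7 m, 17 per group:

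| r | SD of change (m) | Power |
|---|---|---|
| 0.5 | 147.0 | 10% |
| 0.7 | 113.9 | 14% |
| 0.8 | 93.0 | 18% |
| 0.9 | 65.7 | 32% |
| 0.95 | 46.5 | 56% |

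**6. Number recruited.** Allowing for 20% loss, 17/(1 − 0.2) = 21.25, so 22 per group, not 20. Twenty per group with 20% loss leaves 16. Three groups of 20 make 60, not the 72 in the abstract.

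**7. Difference detectable with 90% power** (change scores, t-test):

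| Evaluable per group | r = 0.7 | r = 0.9 |
|---|---|---|
| 16 | 135 m | 78 m |
| 17 | 131 m | 75 m |

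As shares of 347 m these run from about 22% (75/347) to 39% (135/347).

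**The case against.** The best defence is that 147 m is the spread of 6 MWD between patients, while the section speaks of changes and the analysis is repeated-measures. A smaller SD of change may therefore have been used, and a condensed article could leave it to the full protocol. Part of this stands. The 10% power belongs to the printed SD and is not established for the planned analysis. A reader might infer that the trial's true power is 10%, or that a non-significant result is the expected outcome. The documents support neither: power rises with the within-patient correlation, to about 56% at r = 0.95 with 17 per group. The defence does not rescue the stated figure, however. It needs a correlation of about 0.98 that appears nowhere, and it leaves the exact match with a power of 0.10 to coincidence.

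A reader might also object to choosing 6 MWD as the more variable outcome because the two SDs are in different units. That does not hold: means are printed too, and the coefficients of variation are 147/347 = 42% for 6 MWD and 3.2/11.1 = 29% for PWV. Nor can PWV be declared underpowered for a 10% change, because the protocol sets no PWV target.

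Finally, the fear that a null result would be read as equivalence is conjecture. The stated hypothesis is superiority, and how a null result is worded is a matter of reporting practice, not an error in this section.

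**Conclusion.** The point stands as an arithmetic error. On the printed mean, SD, effect and alpha, 90% power needs about 378 per group, roughly 22 times the stated 17 (378/17 = 22.2), and 17 per group gives about 10%. This rests on a two-sided test, a between-group difference of 34.7 m and the printed SD of 147 m.

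That beta and power were swapped is probable, not proven: both the printed label and the exact reproduction of 17 point to it. An unstated SD of change could raise the power, but at assumed correlations of 0.7 to 0.9 it stays between about 14% and 32% with 17 per group. The claim of 90% power for a 10% improvement should not stand as written.

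**What to change.** Rewrite the Sample size calculation section:

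1. Correct beta to 0.10 (power 0.90) and state whether alpha is two-sided.
2. Say which between-group contrast the 34.7 m refers to. The hypothesis points to intradialytic versus home-based, but a comparison with usual care is also possible; the sponsor must choose.
3. State the SD of change in 6 MWD, or the correlation used to derive it, with its source.
4. Withdraw the claim that 17 per group gives 90% power for a 10% improvement.
5. Reconcile 20 per group (60 in total) with the 72 in the abstract, and correct the withdrawal allowance (17 evaluable requires 22 recruited).
6. Then give the difference detectable with 90% power at the resulting evaluable number per group. The 75–78 m (r = 0.9) and 131–135 m (r = 0.7) above illustrate 16–17 evaluable and should be recomputed, not copied.
7. Give the detectable difference for aortic PWV in the same way, without introducing a target that the protocol does not set.

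The cost is one rewritten paragraph and a less favourable power statement. No additional patients need be enrolled.

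### The abstract plans 72 patients and the sample-size section plans 60; the lower figure also falls slightly short of the plan's own withdrawal allowance

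*Protocol article*

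**What the plan says.** The abstract (Methods and design) gives the trial size as a total: "A total of 72 hemodialysis patients will be randomised". It names three arms: "either six months of intradialytic exercise training, home-based exercise training or usual care".

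The section Sample size calculation works per group. It concludes "we require 17 subjects per group" and then adds "Allowing for a 20% withdrawal rate we aim to recruit 20 patients per group". It gives no overall total and does not show how 17 becomes 20.

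Two other sections bear on the point. Randomization describes who generates the sequence and by what means, but gives no allocation ratio. Withdrawal from study says that patients who withdraw will be asked to agree to further testing, so that an intention-to-treat analysis is possible. It gives no expected uptake.

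**The concern.** The planned sample size is the benchmark for ending accrual and for judging afterwards whether the trial reached its target. With two values in force, closing at 60 is complete by the sample-size section and 12 short by the abstract. A stop anywhere between the two could be defended after the event. Twelve patients are 12/72 = 17% of the larger target.

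The second question is whether the lower figure does what its own sentence claims, namely protect 17 patients per group against a 20% loss.

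**Working it through.** **Inputs**

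- Total in the abstract: 72, in 3 arms.
- Required per group (Sample size calculation): 17.
- Withdrawal allowance (same section): 20%.
- Recruitment per group (same section): 20.
- Alpha 0.05, sidedness not stated; intended power 90%.

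**Step 1: the two totals**

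- Sample-size section: 3 × 20 = 60.
- Abstract: 72, which is 72/3 = 24 per group if allocation is equal (an assumption, since no ratio is given).
- Difference: 72 − 60 = 12 patients, or 4 per group.

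The total of 60 does not depend on the ratio, because 20 in each of three groups is 60.

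**Step 2: trying to reproduce the 20 from 17 and 20%**

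- Formula that leaves n after a proportional loss d: n/(1 − d) = 17/0.80 = 21.25, rounded up to 22 per group, 3 × 22 = 66 in all.
- Common shortcut: n × (1 + d) = 17 × 1.20 = 20.4, rounded up to 21.

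Neither gives 20 when rounded up as usual. Twenty is exactly what a 15% allowance would give: 17/0.85 = 20.

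**Step 3: what each target leaves after 20% loss**

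| Total | Per group | Left after 20% loss | Largest loss that keeps 17 |
|---|---|---|---|
| 60 | 20 | 20 × 0.80 = 16.0 | 1 − 17/20 = 15% |
| 66 | 22 | 22 × 0.80 = 17.6 | 1 − 17/22 = 23% |
| 72 | 24 | 24 × 0.80 = 19.2 | 1 − 17/24 = 29% |

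Only 60 falls below 17.

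**Step 4: what the shortfall costs in power**

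Power at 16 per group cannot be computed directly, because the article does not give the standard deviation of the change. It can be found relative to the plan's own claim. Assume that 17 per group gives exactly 90% power in a two-group comparison (normal approximation). The standardised effect then scales with √(16/17) = 0.970.

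- Two-sided: (1.960 + 1.282) × 0.970 − 1.960 = 1.185, which is a power of about 88%.
- One-sided: (1.645 + 1.282) × 0.970 − 1.645 = 1.194, also about 88%.

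The loss is about 2 percentage points under either reading of alpha.

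**The case against.** **The two numbers might describe different things.** A reader might take one as enrolment and the other as completers. The wording rules this out. The 72 are to be randomised, and the 20 per group is a recruitment figure that already includes the withdrawal allowance. A trial cannot randomise more patients than it recruits.

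**The flow chart might settle it.** Figure 1 is not shown and may carry group numbers. It could show which total was intended, but it could not remove the conflict between the two printed statements.

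**The shortfall is trivial, and withdrawal is not the same as lost data.** Much of this stands. The gap is one patient per group after losses, or two recruits per group. Continued testing of withdrawn patients may recover some outcomes. This softens the shortfall but does not remove it: continued testing needs the patient's agreement, no retention rate is given, and the sample-size section itself treats withdrawal as a loss to be allowed for.

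**Stronger readings that the article does not support**

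- That 72 is right and 60 is the slip, or that the allowance was applied twice because 60 × 1.2 = 72. No derivation is given for either total.
- That both totals are inadequate. On the stated inputs, 72 more than covers the 17.
- That the inflation error leaves the trial seriously underpowered. Its effect is about 2 points of power.

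**Conclusion.** The contradiction is established: two current statements of the planned size, 72 and 60, differ by 12 patients and nothing shown reconciles them. The inflation error is real but secondary. On the stated inputs 22 per group (66) are needed, while 20 per group leaves 16 and covers a loss of only 15%.

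This should be corrected, but it does not by itself invalidate the design. The conclusion assumes that withdrawn patients contribute no outcome data, that the 72 would be split equally, and, for the 88%, that 17 per group delivers 90%. The 17 is taken as stated. Whether it follows from the printed mean and standard deviation is a separate question, so saying that a total covers the 17 is a statement about consistency only, not evidence of adequate power.

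**What to change.** The sponsor should identify the target that was actually planned and state it identically in the abstract and in Sample size calculation, with the total, the number per group and the inflation shown as n/(1 − 0.20).

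- **If 72 was planned:** change the per-group figure to 24 (assuming equal allocation) and state that about 19 per group are expected after 20% withdrawal, which covers the 17.
- **If 60 was planned:** correct the abstract. Then either state that 16 per group are expected after 20% withdrawal, with power slightly below 90% (about 88% if 17 per group gives 90%), or state that the allowance is 15%.

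A rationale for either number should be the one the sponsor actually used, not one fitted to the figure afterwards.

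The cost is a sentence or two of text. Stating the planned target changes no enrolment. Adopting 72 when 60 was planned would add 12 patients, and this point does not ask for that.
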